### Data management

A comprehensive data protection concept was developed with the data protection officer of the German Pension Insurance North and clarifies the data processing, rights of participating persons, and technical and organizational measures to ensure the secure and confidential collection, processing, and storage of data. Administrative data are provided by the German Pension Insurance North. Personal data is removed, replaced with the unique study identifier, and submitted to the principal investigator. Questionnaire data are entered, reviewed and exported to statistical software packages for further analysis. Data input and data verification are performed by trained research assistants. The administrative and questionnaire data will be linked using a unique study identifier. Access to the data is limited to the authors and research assistants on the research team, and data management is performed by the authors.

### Statistical methods

We will use Cox regressions to analyze our primary outcome and our time-to-event secondary outcome (i.e., disability pension) and report hazard rate ratios and 95% confidence intervals. Poisson regressions with baseline adjustments will be calculated to estimate incidence rate ratios and 95% confidence intervals in our analysis of our continuous secondary outcomes. We will use linear regressions to analyze our continuous tertiary outcomes. The use of administrative data will ensure that all individuals can be included in our analysis as randomized (intention-to-treat).

Subgroup analyses examine whether estimates differ for the first and second cohorts of participants. The analysis of our nested cohort study of case management participants only will describe the implementation of the case management intervention and changes during the case management intervention. We will use paired t-tests for continuous outcomes and McNemar tests for binary outcomes when analyzing the change between the start and end of the case management intervention.

Analyses of our primary and secondary outcomes will not be affected by non-responses or patient withdrawals due to the use of administrative data, but tertiary outcomes may be missing due to non-response or incomplete response to the 12-month follow-up questionnaire. We will use multiple imputation to augment incomplete responses to the 12-month follow-up questionnaire.

We will not perform interim analyses and did not specify a stopping rule. Statistical test will be regarded as significant if the two-sided p-value of a test is less than 0.05. An up-to-date version of Stata (StataCorp, College Station, Texas, USA) will be used to conduct analyses.

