### Sample size

We will include 9000 persons (intervention group: *n* = 4500; control group: *n* = 4500) in order to detect an increase in claiming a rehabilitation from 10 to 12% in the intervention group (two-sided type I error rate: 5%, power: 80%). We expect that 12.5% of individuals who are informed about our case management intervention will contact our case managers. Of whom, half will join the one-on-one interview, and of whom, 80% will start a case management intervention. This is in line with our pilot study showing that about 5% of the informed individuals participated in a case management intervention. About half of them are anticipated to claim rehabilitation.

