### Blinding

Case management intervention participants will be fully aware of their group assignment when we ask them to contact our case managers. Participants in the control group will not learn their group assignment until we ask them to complete the questionnaires to collect tertiary outcomes data. Primary and secondary outcomes data are generated by the data department of the pension insurance agency without knowledge of group assignment. The principal investigator and data analysts will be aware of group assignments when analyzing the data. Unblinding of the control group before assessing tertiary outcomes data is not intended.

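### Multiple imputation is stated only for incomplete questionnaires, so the tertiary comparisons, read plainly, are among responders, and differential response could bias them by about as much as the diluted effect

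*Protocol article*

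**What the plan says.** In the protocol article, Statistical methods recognises that "tertiary outcomes may be missing due to non-response or incomplete response to the 12-month follow-up questionnaire". The next sentence gives the remedy: "We will use multiple imputation to augment incomplete responses to the 12-month follow-up questionnaire". The analysis model is stated as "We will use linear regressions to analyze our continuous tertiary outcomes".

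The same section supports intention-to-treat in these terms: "The use of administrative data will ensure that all individuals can be included in our analysis as randomized (intention-to-treat"). That support comes from administrative records. According to Table 2 these hold the primary and secondary outcomes; the patient-reported tertiary outcomes come from the survey.

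On the survey itself:
- Data collection describes one postal questionnaire 12 months after random assignment, with a single reminder after three weeks. No expected response rate is given.
- Trial design says everyone is told about the study and invited to the survey at one year.
- Blinding says: "Participants in the control group will not learn their group assignment until we ask them to complete the questionnaires to collect tertiary outcomes data".
- Sample size and Recruitment expect about 5% of the intervention arm, 225 people, to enter case management.

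**The concern.** The section separates two ways in which a tertiary outcome can be missing and then provides for one of them. People who return no questionnaire fall under the first, for which no method is stated.

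This matters because of the Zelen design. Controls have had no contact with the study when the questionnaire arrives. The intervention arm was written to up to a year earlier, and a small part of it has been offered up to 50 hours of personal case management (Table 1). Those participants may be readier to answer. Their counterparts in the control arm, the people who would have taken up the offer, have no such reason. Participants may then be over-represented among intervention responders with nothing to balance them among control responders.

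At 5% uptake, any intention-to-treat effect on a patient-reported scale is heavily diluted, so even a modest selection bias can be comparable with it. Several tertiary scales would be read against p < 0.05.

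**Working it through.** **Inputs from the article.** 4500 per arm. 12.5% of those informed make contact, half of these attend the interview, and 80% of these start case management. Two-sided 5% level.

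**Inputs that are assumed.** Response rates, the difference between participants and others, and the strength of selection. The article gives none of these, nor any expected tertiary effect.

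**Step 1: the article's uptake figure.** 0.125 × 0.5 × 0.8 = 0.05, and 0.05 × 4500 = 225. This reproduces the stated 5% and 225.

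**Step 2: diluted effect.** Intention-to-treat effect = uptake × effect among participants.
- 0.05 × 0.2 SD = 0.010 SD
- 0.05 × 0.5 SD = 0.025 SD
- 0.05 × 0.8 SD = 0.040 SD

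**Step 3: bias when participants respond more often.** Let q be response among participants, r response among everyone else in both arms, and D the difference between participants and others before any effect.

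Share of participants among intervention responders: s = 0.05q / (0.05q + 0.95r). Bias = (s − 0.05) × D.

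| q / r | s | Bias, D = 0.5 SD | Bias, D = 0.2 SD |
|---|---|---|---|
| 50% / 30% | 0.025/0.310 = 8.1% | 0.015 | 0.006 |
| 60% / 30% | 0.030/0.315 = 9.5% | 0.023 | 0.009 |
| 70% / 25% | 0.035/0.2725 = 12.8% | 0.039 | 0.016 |
| 80% / 20% | 0.040/0.230 = 17.4% | 0.062 | 0.025 |

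Over-representation also magnifies a real effect. At 80%/30%, s = 0.040/0.325 = 12.3%. A 0.5 SD gain in participants would then show as 0.123 × 0.5 = 0.062 SD instead of 0.025 SD.

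**Step 4: a second model, with response depending on the outcome.** Let P(response | Y) = expit(a + bY), with Y standard normal, no treatment effect, and a set separately to give each arm's response rate. The table shows the absolute difference between the two responder means, in SD.

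| Response odds ratio per SD | 30% vs 32% | 30% vs 35% | 30% vs 40% |
|---|---|---|---|
| 1.1 | 0.002 | 0.005 | 0.010 |
| 1.25 | 0.005 | 0.011 | 0.022 |
| 1.5 | 0.008 | 0.020 | 0.040 |
| 2.0 | 0.014 | 0.034 | 0.067 |

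With equal response and equal selection in both arms the bias is zero.

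**Step 5: effect on the test.**
- At 30% vs 35% and odds ratio 1.5, SE = √(1/1350 + 1/1575) = 0.0371 SD and bias/SE = 0.0202/0.0371 = 0.54. The false-positive rate rises from 5% to about 8.5%.
- At 30% vs 40%, SE = √(1/1350 + 1/1800) = 0.0360 SD and bias/SE = 0.0402/0.0360 = 1.12. The false-positive rate is about 20%.

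**Step 6: set against precision.** At 30% response in both arms, the difference detectable with 80% power is (1.96 + 0.84) × √(2/1350) = 0.108 SD. This exceeds every bias above.

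**The case against.** **The article does not say that non-responders are excluded.** This stands. A reader might infer that they are certain to be dropped, but no sentence defines the tertiary analysis set, the imputation wording may be loose, and an analysis plan that is not shown may settle it. Even so, the two causes are named separately and the stated rule then covers one of them. The plain reading is a rule that stops short, which is more than silence.

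**The size rests on assumptions.** This also stands. A reader might infer that the bias is as large as any plausible effect. The documents do not support that:
- Two of the four scenarios in Step 3 fall below the 0.025 SD benchmark even with D = 0.5 SD.
- With weak selection (odds ratio 1.1 to 1.25) and a gap of 2 to 5 points, the bias is only 0.002 to 0.011 SD.
- If all 12.5% who make contact gained 0.5 SD, the diluted effect would be 0.0625 SD, about level with the largest bias in Step 3.

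**The survey procedure might be blamed.** A reader might infer that the cover letters differ by arm, or that disclosure of group drives response. Data collection describes the same mailing and reminder for everyone. Blinding also says that unmasking controls before tertiary assessment is not intended, and the intervention arm already knows its assignment. No change to letters or disclosure follows.

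**The consequence is limited.** Agreed. Only tertiary outcomes are touched, and the biases are small against what the survey could detect.

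**Conclusion.** The concern holds in a limited form. The stated missing-data rule covers one of the two causes that the article itself names, and the intention-to-treat statement rests on data that contain no tertiary outcomes. As written, the tertiary regressions compare responders in a design where response may differ by arm and by case-management participation.

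Under moderate differential response the bias may be of the same order as the diluted effect: about 0.015 to 0.06 SD if participants differ by 0.5 SD, against about 0.01 to 0.04 SD at 5% uptake. It is smaller with weaker selection and absent if response and selection are equal in both arms. All response rates, the 0.5 SD difference and the odds ratios are assumptions. Primary and secondary outcomes are unaffected. This is a cheap improvement to the tertiary analysis and does not threaten the trial's main conclusion.

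**What to change.** Extend the missing-data method for tertiary outcomes to all 9000 randomised persons. Use either inverse-probability-of-response weights or multiple imputation that includes non-responders, fitted separately by arm. Predictors should be:
- the administrative baseline data (age, gender, risk index score, benefit history);
- the 12-month administrative outcomes;
- in the intervention arm, case-management participation.

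Report response rates by arm, show the responder-only analysis alongside, and add a missing-not-at-random sensitivity analysis.

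In the 70%/25% scenario of Step 3, weighting by participation gives 0.035/0.70 = 0.05 for participants and 0.2375/0.25 = 0.95 for others. The 5% share is restored and that bias is removed.

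The data are largely in place. Data management links administrative and questionnaire data by study identifier. Case management needs the insurer's approval and is documented by the case managers, so participation should be known for the whole intervention arm.

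The cost is more analysis work and somewhat wider intervals. The correction works only as far as these variables explain both response and outcome. Table 1 lists the baseline questionnaire with the one-on-one interview, so most randomised persons would seem to have no baseline patient-reported values to draw on. That is why the sensitivity analysis is needed.

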## Discussion

The purpose of our large-scale randomized controlled trial is to test the effects of a new multi-component strategy for individuals with a high risk of receiving a disability pension developed to improve coverage of rehabilitation and the coordination of support for people with chronic diseases and disabilities. We provide updated information on our trial website www.aktifame.de. All results of our study will be published as articles in peer-reviewed journals and at conferences. The authors of this protocol will write the final trial publications. The use of professional writers is not intended. The researchers and the German Pension Insurance North will design a flyer providing information about the key findings of our study (circulation: 2000 copies). These will be sent out nationwide. We will also host a symposium to provide information about our study.

The study protocol was designed using the SPIRIT (Standard Protocol Items: Recommendations for Interventional Trials) checklist [30].

### Trial status

Recruitment has started and is ongoing.

## Abbreviations

AktiFAME: Active access, counseling, and case management for people at high risk of permanent work disability
F-SozU K-6: 6-item brief form of the Perceived Social Support Questionnaire (Fragebogen zur Sozialen Unterstützung)
HEALTH-49: Hamburg modules for the assessment of general aspects of psychosocial health for therapeutic practice (Hamburger Module zur Erfassung allgemeiner Aspekte psychosozialer Gesundheit für die therapeutische Praxis)
IMET: Index for the measurement of limitations of participation (Index zur Messung von Einschränkungen der Teilhabe)
PSS-10: Perceived Stress Scale
SOEP: Socio-Economic Panel
SPE: Self-reported prognosis of employability
SPIRIT: Standard Protocol Items: Recommendations for Interventional Trials
TIDieR: Template for Intervention Description and Replication
WAS: Work Ability Score
